#### Interim analyses {21b}

Not applicable in this study as interim analysis will not be performed.

#### Methods for additional analyses (e.g., subgroup analyses) {20b}

For exploratory analysis, we hypothesize that GPs might use the CDSS in a better way when they have used the system for a while and those having higher uptake with the CDSS might have larger effect with participants. Complex participants, with more pain sites, higher severe symptoms, and/or poorer prognosis might have larger effect of the CDSS. Therefore, we will do exploratory analysis of these pre-specified subgroups:The first 9 recruited participants compared to the participants numbered 10 and above for each GPParticipants with two or less MSK pain sites versus participants with 3 or more MSK pain sites at baselineParticipants with less than 1.85 points versus participants with 1.85 points or higher in Hopkins Symptom Checklist (HSCL-10) at baselineParticipants with scores < 8 vs ≥ 8 on the work ability scale at baselineBased on user data of the CDSS (clicks in the CDSS); GPs with number of clicks in the lower vs the upper quartile in the intervention group to see if higher uptake of the CDSS is importantComparing effectiveness in the five phenotype groups as defined by our previous work [27]

We will carry out exploratory subgroup analyses to assess for treatment effect heterogeneity for each of the subgroup categorizations defined above. For these analyses, separate mixed logistic regression models will be extended to include each subgroup and an interaction term between treatment allocation and the subgroup. The estimated treatment effect will be estimated and reported for each subgroup. The interaction term will be used for assessing the presence of treatment effect heterogeneity where the comparison is between two subgroups. For the assessment of treatment effect heterogeneity based on the five phenotype groups, overall treatment effect heterogeneity will be assessed based on a likelihood ratio test comparing the models with and without the interaction term. Comparison of treatment effect between phenotype pairs will be considered if the likelihood ratio test indicates an overall treatment effect heterogeneity.

These analyses are considered to be exploratory as the trial was not powered for subgroup analyses. The results from all subgroup analyses will be presented in either the manuscript or supplementary files.

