#### Design and content of the CDSS

The CDSS is designed as a standalone, computerized system with a backend hosted entirely on servers located at Norwegian University of Science and Technology. The description of the backend and the technical setup is beyond the scope of the protocol. The GPs can access the CDSS through a clinical dashboard in their web browser. The CDSS is developed based on experiences from an ongoing trial in a physiotherapy setting and adapted to GP practice. The content and the layout of the screens have been developed in close collaboration with GPs, patients, researchers, and web designers. The GPs and patients contributed to the design by reviewing “mock-ups” and suggesting placement, coloring, and important factors shown in the intervention. Furthermore, the GPs contributed with treatment suggestions and advice on how to build the automated summary of patient subjective history, clinical examination, and chosen treatment. This to adapt the CDSS to the GP workflow and to make it easy to read also for the patient as a part of shared decision making and to improve fidelity to the system among the GPs. The clinical dashboard of the CDSS consists of four main screens: (1) login and patient overview, (2) patient profile, (3) clinical examination, and (4) treatment recommendations. The CDSS for stratified care is summarized in Fig. 2.

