#### The clinical examination screen

The clinical examination screen is where the GP reports the main complaint (neck, shoulder, back, hip, knee, or widespread pain) and registers a few clinical tests relevant to the main complaint. Furthermore, the GP registers the ICPC-2 diagnosis, primary and secondary, if applicable. The results from the clinical examination are not integrated in the treatment recommendation provided by the CDSS.

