#### GP`s workflow in the CDSS

The GPs are instructed in how to use the CDSS in their clinical practice and educated in the theoretical basis for the stratified care approach and the implications of the biopsychosocial phenotypes. The participant completes the questionnaires before the appointment with the GP. When the participant has completed the baseline questionnaires, the information is made available for the GP in the CDSS. The GPs are instructed to use the CDSS together with the participant during the consultation and involve the participant in all parts of the CDSS.

The GP starts by opening the patient profile in the CDSS. The GP can then use the patient profile to prepare for the appointment and together with the participant during the consultation. As the patient profile displays several aspects of their subjective history, including biopsychosocial phenotype, pain drawing, expectations, etc., it is recommended that the GP shows the patient profile to the patient and that they choose what to focus on in the current appointment. The GPs are also instructed to ask the participants if they feel that the patient profile properly represents their complaints.

After taking the patient subjective history and using the patient profile together with the participant, the next part of the consultation is the clinical examination. The GP opens the clinical examination screen and records the participant’s main complaint. They then perform the relevant examinations and register the findings and the primary and secondary ICPC-2 diagnosis in the clinical examination screen.

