#### Control group

The control group will receive current care by the GPs randomized to this arm. Usual primary care for MSK pain complaints is known to be variable; for example, some participants may receive advice, prescriptions for medications, and nothing more, some may be asked to return to the GP for follow-up assessment or treatment, whereas others may be referred to other services, including tests and investigations, or treatment services such as physiotherapy, orthopedics, or pain clinics. Participants will answer the same questionnaires as the intervention group at all data collection time points. The GPs in the control group will have access to the login and patient overview and the clinical examination screen. The control group will not have access to the patient profile or the treatment recommendation screen.

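### CDSS uptake is defined as a GP's number of clicks with no scaling to participants recruited, so the uptake contrast is confounded with recruitment volume

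*Protocol article*

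**What the plan says.** The section on additional analyses {20b} in the Protocol article lists six subgroup comparisons. One is based on user data from the CDSS and contrasts "GPs with number of clicks in the lower vs the upper quartile" in the intervention group; its stated aim is to find out whether greater uptake is important. The source (clicks), the unit (the GP), the quantity (a number) and the cut (quartiles) are thus all fixed. Neither a denominator nor a restriction to particular screens is stated. The same section adds: "These analyses are considered to be exploratory as the trial was not powered for subgroup analyses".

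The section on the GP's workflow describes use of the system one participant at a time: "The GPs are instructed to use the CDSS together with the participant during the consultation". Table 1 places the CDSS at week 0 for each participant. The section on sample size {14} plans 22 GPs per arm with 17 participants each.

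**The concern.** Uptake, as the protocol means it, is how fully a GP uses the system with the patients for whom it is available. A raw click count also rises with the number of those patients. Two GPs who use the CDSS identically in every consultation will have different counts if one recruits more than the other, and may fall in opposite quartiles.

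The article gives reasons to expect unequal recruitment. GPs are randomised in two batches and drop-outs are replaced from a waiting list (Sequence generation {16a}), so the time available to recruit may differ. A weekly prize goes to the GP who recruits most (section {18b}). The Discussion warns that workload may reduce recruitment.

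What is at stake is interpretation. The Introduction names poor GP fidelity as a limitation of an earlier stratified-care trial and as a reason for building the CDSS. If the main result is null, readers may use this contrast to separate a system that does not work from one that was not used. With an unscaled count, a difference between the quartiles could also reflect how GPs who recruit many patients differ from those who recruit few.

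**Working it through.** **The plan's own figures.** The click contrast has no figure of its own. The sample size does reproduce: 170 per arm for 50% versus 65% (two-sided 5%, 80% power), times the design effect 1 + (14 − 1) × 0.05 = 1.65, gives 280.5 against the stated 280; and 44 × 17 = 748. This does not bear on the click metric, but it supplies the 22 GPs and the mean of 17 participants used below.

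**Identity.** For one GP let m be participants recruited and c the average clicks per participant. The count is T = m × c. At equal c, the ratio of two GPs' counts is simply the ratio of their recruitment. This needs no assumption.

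**Share of the ranking due to recruitment.** On the log scale, log T = log m + log c. If m and c are independent and log-normal with coefficients of variation CVm and CVc, then Var(log m) = ln(1 + CVm²), likewise for c, and

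share from recruitment = ln(1 + CVm²) / [ln(1 + CVm²) + ln(1 + CVc²)].

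The protocol gives neither CV, so each was varied from 0.2 to 1.0 (an assumption). Examples:
- CVm = CVc = 0.4: 0.148 / (0.148 + 0.148) = 50%.
- CVm = 0.4, CVc = 0.2: 0.148 / (0.148 + 0.039) = 79%.
- CVm = 1.0, CVc = 0.2: 0.693 / (0.693 + 0.039) = 95%.
- CVm = 0.2, CVc = 1.0: 0.039 / (0.039 + 0.693) = 5%.

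**Effect on the quartiles.** 20,000 sets of 22 intervention GPs were simulated with mean recruitment 17. Since 22 / 4 = 5.5, the top six and bottom six GPs by T were compared. Ratios are medians of upper over lower group. The last column is the share of the top group that would also be in the top six on clicks per participant, taken over 3,000 of the sets.

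| CVm | CVc | Recruitment share | Ratio of mean recruits | Ratio of clicks per participant | Top-group overlap |
|---|---|---|---|---|---|
| 0.2 | 1.0 | 5% | 1.11 | 6.66 | 87% |
| 0.4 | 0.65 | 30% | 1.63 | 3.20 | 71% |
| 0.4 | 0.4 | 50% | 1.89 | 1.89 | 61% |
| 0.4 | 0.2 | 79% | 2.23 | 1.24 | 47% |
| 1.0 | 0.2 | 95% | 6.70 | 1.11 | 36% |

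In every scenario the upper group has more recruits per GP than the lower. Recruitment outweighs clicks per participant only where it is the more variable of the two. A positive correlation between m and c would widen the recruitment gap between the groups, and a negative one would narrow it.

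**The case against.** The strongest reply is that the article says number of clicks, not total clicks, and defers detail to a statistical analysis plan that is not shown and may scale the count. That is possible. But the article does more than leave the measure open: it pre-specifies unit, quantity and cut, and a count without a denominator is its natural reading. If the analysis plan scales it, the two texts should be made to agree.

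Several stronger readings are tempting and are not supported:
- *The contrast mostly compares high and low recruiters.* The documents give no spread for recruitment or for clicks per participant. The 5% to 95% range shows that this may or may not be so.
- *Clicks are the trial's only measure of what was delivered.* They are not. Treatment plans are registered in the CDSS, treatment up to 3 months goes into a case report form, Table 2 includes adherence to the treatment plan, and adequacy of care and a process evaluation are planned.
- *The count is invalid because it includes screens that control GPs also have.* Of the four screens, "1) login and patient overview, (2) patient profile, (3) clinical examination, and (4) treatment recommendations", the first and third are indeed open to controls, while "The control group will not have access to the patient profile or the treatment recommendation screen". But the contrast lies within the intervention arm, where the examination screen is a step in the CDSS workflow. That "The results from the clinical examination are not integrated in the treatment recommendation provided by the CDSS" makes its clicks a weaker sign of stratified-care use, not an error to count. This is a secondary refinement.
- *It duplicates the subgroup of the first 9 participants versus later ones.* That split is made within each GP; the click contrast is between GPs.

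Cumulative use could also be defended as a measure of experience. However, the protocol attaches the click contrast to uptake and covers experience with the first-9 split.

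**Conclusion.** The point holds in limited form. As written, the uptake measure is a GP-level click count not scaled to participants recruited, so the contrast is confounded with recruitment volume. That confounding follows from the identity above once recruitment differs between GPs. Its size does not: recruitment supplies about half of the variance of log clicks if the two spreads are equal, and 5% to 95% over the assumed range, with independence and log-normal distributions assumed throughout.

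The consequence is confined to one exploratory, unpowered subgroup contrast. A reader might infer that the trial's conclusions are at risk; they are not, because no primary or secondary analysis uses the click count. It is a minor point, worth correcting because the correction is nearly free.

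**What to change.** In section {20b}, define uptake per enrolled participant. Either of these would serve:
- a GP's clicks in the CDSS divided by the number of participants that GP enrolled; or
- the share of a GP's enrolled participants for whom a treatment plan was registered in the CDSS.

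Where the logs can be split by screen, report the measure also for the patient profile and treatment recommendation screens alone. Show the number of participants per GP in each uptake group, so that readers can see any remaining imbalance.

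The cost is a change of wording and minor extra log processing. The first version needs only the click counts and enrolment numbers. The screen-level version is conditional, because the protocol does not say how clicks are logged. Scaling does not make the comparison causal: uptake per participant is still a post-randomisation characteristic of GPs, and the result should be reported as exploratory and non-randomised. Patients and trial conduct are unaffected.

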#### Analysis of the primary outcome

The effect of CDSS at 3 months will be estimated for both primary outcomes using three-level mixed logistic regression models. Each primary outcome will be assessed in a separate model that includes the repeated measures of the outcome at 2 weeks, 4 weeks, 8 weeks, and 3 months follow-up as the dependent variable and such that they are clustered by follow-up timepoint (level 1), participants as level 2, and GPs as level 3. Treatment allocation, time point, and an interaction between treatment allocation and time point will be included as independent variables. We will adjust for the stratification variable and possible prognostic variables (age, sex, education, and pain-duration). In addition, when analyzing PSFS, we will adjust for the baseline value.

The treatment effect will be estimated for each time point from the mixed logistic regression models and presented as an OR with 95% confidence intervals.

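### The click-quartile subgroup exists only in the intervention arm, so the treatment-by-subgroup interaction prescribed for it cannot be estimated

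*Protocol article*

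**What the plan says.** Section {20b} of the protocol article lists six categorisations: recruitment order within GP, number of pain sites, HSCL-10 score, work ability, CDSS clicks, and phenotype. The clicks entry contrasts "GPs with number of clicks in the lower vs the upper quartile in the intervention group" and is meant to show whether greater uptake matters.

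The same section then commits to "assess for treatment effect heterogeneity for each of the subgroup categorizations defined above". The method is that "separate mixed logistic regression models will be extended to include each subgroup and an interaction term between treatment allocation and the subgroup". For two-level categorisations, "The interaction term will be used for assessing the presence of treatment effect heterogeneity where the comparison is between two subgroups"; only the five phenotypes get a different test, a likelihood ratio test. A treatment effect is also to be reported for each subgroup. All of this is labelled exploratory and unpowered.

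The model being extended is described under the analysis of the primary outcome: "The effect of CDSS at 3 months will be estimated for both primary outcomes using three-level mixed logistic regression models". Its dependent variable is the "repeated measures of the outcome at 2 weeks, 4 weeks, 8 weeks, and 3 months follow-up", and "Treatment allocation, time point, and an interaction between treatment allocation and time point will be included as independent variables".

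On the control arm, the article says "The GPs in the control group will have access to the login and patient overview and the clinical examination screen". It adds that these GPs cannot open the patient profile or the treatment recommendations.

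**The concern.** A treatment-by-subgroup interaction asks whether the difference between arms is larger in one subgroup than in another, so each subgroup needs members in both arms. Four of the other five categorisations rest on baseline patient data and the fifth on recruitment order, so all five exist in both arms. Click quartiles are defined inside the intervention arm only.

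The test named in advance therefore cannot be run for clicks, and some substitute would have to be chosen after the data are in. The obvious substitute, high-click against low-click GPs, is not protected by randomisation. GPs who click more may differ in interest, workload or patient mix, and clicks are themselves a consequence of how the trial unfolds. If the result appears beside the interaction analyses as one more test of treatment-effect heterogeneity, it will look like evidence of a kind it is not.

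**Working it through.** **Inputs.** Subgroup definition and model: section {20b} and the analysis of the primary outcome. Numbers of GPs and participants, ICC and cluster size: sample size section {14}. Screens open to control GPs: control group section.

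**The plan's own figures.** 22 GPs per arm × 17 participants = 374 per arm; 374 × 2 = 748, as stated.

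**1. Can the interaction be estimated?** Let T be treatment (0/1) and H the upper click quartile (0/1). The fixed effects are intercept, T, three time indicators, three T × time terms, H and T × H, which makes 10 columns (covariates aside). There are three ways to code the control GPs, who have no H:

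- H = 0 for all controls. Then H = T × H in every row: 10 columns, rank 9.
- H = 1 for all controls. Then H = 1 − T + T × H in every row: again rank 9.
- H missing, so controls drop out. Then T = 1 throughout. T repeats the intercept, T × time repeats time and T × H repeats H. Only intercept, three time terms and H remain: rank 5.

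No coding identifies T × H. A baseline subgroup present in both arms gives rank 10 of 10, so the failure is specific to clicks.

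**2. What can be estimated, and how well?** Upper against lower quartile within the intervention arm, or each quartile against all controls. Neither is a randomised comparison.

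- GPs per quartile: 22 / 4 = 5.5, so 5 or 6. GPs used: 2 × 5.5 = 11 of 22.
- Participants per quartile: 5.5 × 17 = 93.5 recruited, or 5.5 × 14 = 77 at the cluster size used for power.
- Design effect: 1 + (14 − 1) × 0.05 = 1.65. Effective number: 77 / 1.65 = 46.7 per quartile.
- Approximate 95% half-width for a difference in proportions at one time point, assuming both are near 0.50: 1.96 × √(2 × 0.25 / 46.7) = 0.20.

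That is about ±20 percentage points, against the 15-point difference for which the whole trial is sized. With 5 or 6 clusters a side, this normal approximation is optimistic.

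**3. Secondary point: the time dimension for the other five categorisations.** The stated extension contains T × H but no T × H × time, so it fits one subgroup difference to all four time points. The table compares that common term with the 3-month value (log ratio of odds ratios) under assumed patterns, using expected-data logistic fits.

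| Assumed difference at weeks 2 / 4 / 8 / 12 | Common term | 3-month value |
|---|---|---|
| 0.6 / 0.6 / 0.6 / 0.6 | 0.60 | 0.60 |
| 0 / 0.2 / 0.4 / 0.6 | 0.32 | 0.60 |
| 0 / 0 / 0 / 0.8 | 0.20 | 0.80 |
| 0.8 / 0.8 / 0.8 / 0 | 0.60 | 0 |

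Adding T × H × time recovers the 3-month value in every row. A rough simulation shows the price (44 GPs of 17, marginal logistic model clustered by GP, 60 runs per pattern, assumed effects). Under the constant pattern the common term was rejected in 75% of runs and the 3-month term in 42%, with mean standard errors of 0.19 and 0.29 (ratio about 1.5). With heterogeneity only at 3 months the rates were 12% and 53%; with it only at weeks 2 to 8 they were 70% and 5%. With no heterogeneity both terms were rejected in 10% of runs, so these rates are indicative only.

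**The case against.** **On clicks.** Control GPs use two CDSS screens, so some control clicks may be logged. This does not rescue the interaction: the quartiles are defined in the intervention arm, and clicks on the login and examination screens say nothing about uptake of the two withheld screens. It is also true that a treatment effect per subgroup can be produced by setting each quartile against all controls. That fits, but it compares a self-selected set of intervention GPs with all controls, and it is not the interaction the plan names. The fair part of the objection is about scale: one of six analyses, all exploratory, with nothing confirmatory resting on it. Whether clicks are total or per participant is not stated, and the choice of scale and of quartiles is partly preference.

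**On time.** A reader might infer that the subgroup models as a whole miss their target because they do not test heterogeneity at 3 months. The article does not support that. Section {20b} names no time point for the subgroup effects; the 3-month target belongs to the primary analysis. A common interaction over repeated follow-ups is a legitimate choice, and the more powerful one if heterogeneity is constant. The article also defers analysis detail to a statistical analysis plan that is not shown and could add a time term. A reader might further infer that the common term is dominated by early weeks in which an effect is unlikely, and so captures only about half the 3-month difference. That fraction, (2 + 4 + 8 + 12) / 4 / 12 = 0.54, holds only if the difference rises linearly from zero. The article gives no time course for the effect, and under a constant pattern the fraction is 1.

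**Conclusion.** The clicks interaction is wrong as written. The article applies it to every listed categorisation, and for clicks it cannot be estimated under any coding of the control arm. This follows from the definition alone and needs no assumption about effect size. What remains is an observational comparison of about 5 or 6 GPs with 5 or 6 others, with an approximate half-width of 20 percentage points under the article's ICC of 0.05 and 14 participants per GP, and proportions assumed near 0.50.

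The consequence is limited. One exploratory analysis is affected; the primary estimates, the sample size and the other five subgroup tests stand.

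The time structure of those five tests is a choice to be made knowingly, not an error. The common term matches the 3-month difference only under constant heterogeneity. For PSFS the question arises only if the scale is collected at weeks 2, 4 and 8. The outcomes section {12} and the primary analysis say it is; Table 2 marks it only at baseline and weeks 12 and 26. If Table 2 is followed, the averaging concerns GPE alone.

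**What to change.** **Needed.** Remove clicks from the list to which the treatment-by-subgroup interaction applies. Describe it separately as an exploratory, observational analysis of uptake within the intervention arm, and say that GPs are not randomised to uptake. Preferably use clicks per participant, because a raw total also rises with the number of participants a GP recruits. Treating it as continuous would keep all 22 GPs instead of about 11. The cost is wording: no new data and no change to any other analysis.

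**Optional.** For the five categorisations present in both arms, state which time point the subgroup effect refers to. If 3 months is of interest, add subgroup-by-time and treatment-by-subgroup-by-time terms and report the 3-month contrast alongside the common term. The cost is real: in the rough simulation under constant heterogeneity the standard error rose by about half and detection fell from 75% to 42%. Reconcile the PSFS schedule between the outcomes section, the primary analysis and Table 2 first, since that decides whether the question arises for PSFS at all.
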